## Abstract

**Background:**

An unhealthy diet is a well-established risk factor for the development of noncommunicable diseases, and office workers are at a higher risk of noncommunicable diseases due to their sedentary work style. Stage of change (SOC) theory–based and stage-matched interventions effectively influence dietary and behavior changes. The effectiveness of such interventions in the context of low- and middle-income countries is yet to be assessed.

**Objective:**

This protocol describes a cluster randomized trial planned to evaluate the effectiveness of an intervention for changing dietary behavior among government office workers in the Galle district in Sri Lanka.

**Methods:**

A cluster randomized trial was conducted in 20 clusters divided into intervention and control arms. A cluster was an office with 30 clerical-type workers who were sedentary at work. A stage-matched intervention based on behavior change processes was implemented in the intervention clusters for 3 months. Participants were provided with an intervention matched to their SOC at baseline. Precontemplators and contemplators received awareness-raising and emotional arousal interventions. Others received goal setting and self-monitoring interventions. The SOC and dietary intake were assessed at baseline and the postintervention stage through a staging algorithm, and 24-hour dietary recall was supplemented with a picture guide and computer software. Adherence to the intervention was assessed monthly. We hypothesized that participants would achieve a progressive change in the SOC and healthy dietary intake in the intervention clusters compared to the control clusters.

**Results:**

By December 2024, the planned intervention was completed. Data analysis on the effectiveness of the intervention is to be completed and published in 2025.

**Conclusions:**

This protocol reports a stage-matched intervention based on SOC theory, enriching the current knowledge base with new evidence from office workers in a low- to middle-income country.

**Trial Registration:**

Sri Lanka Clinical Trials Registry SLCTR/2020/025; https://slctr.lk/trials/slctr-2020-025

**International Registered Report Identifier (IRRID):**

DERR1-10.2196/70293

## Introduction

### Background

An unhealthy diet, which can be defined as nutritionally of poor quality or harmful to health [1], has a significant and well-established impact on developing noncommunicable diseases (NCDs) and their complications. It was highlighted that an unhealthy diet accounted for 11 million deaths and 225 million disability-adjusted life years in 2017 [2]. The Food-Based Dietary Guidelines (FBDG) for Sri Lankans provide directions on the necessary amount of food intake and dietary practices for a healthy diet [3]. The FBDG for Sri Lankans have 12 recommendations for a healthy diet, including the amount of food to be consumed [4]. The NCD risk factor survey (STEPS survey) conducted in 2015 highlighted that nearly 75% of male and female individuals were not consuming the recommended amount of fruits and vegetables [5]. An unhealthy diet is common among the workforce, and office workers are at higher risk of developing NCDs due to their sedentary lifestyle at work [6]. Studies conducted in the local context have also highlighted the increased prevalence of unhealthy diets among office workers [7,8]. Because working adults spend most of their time at the workplace, and due to the clustering of common risk factors and behaviors in one place, workplace-based interventions are believed to be successful. Several local and global studies have shown the effectiveness of interventions in workplaces [9,10].

Behavior change does not occur randomly, and behavior change theories explain the mechanism of behavior change [11]. The stage of change (SOC) theory describes 5 stages through which individuals can go through in changing their behavior, and it also describes interventions needed to be conducted at each stage to bring about the behavior change [12]. SOC theory is known to be effective in changing physical activity and dietary behavior, smoking and opioid addiction cessation, and dental hygiene improvement [13], whereas stage-matched interventions have been more successful and effective [14-16].

Behavior change techniques (BCTs) are defined as the smallest active ingredients of an intervention [17]. The selection of appropriate BCTs is one of the key factors on which the effectiveness or the success of an intervention depends [18]. Provision of specific instructions on the desired behavior through a credible source, action planning, goal setting (regarding the behavior or outcome), social support, and self-monitoring are commonly used and effective BCTs for interventions aimed at dietary behavior change. Among them, goal setting and self-monitoring have been identified as effective BCTs in different contexts of behavior change interventions [17,19,20].

### Objectives

Sri Lanka is experiencing a huge burden of NCDs, contributing largely to mortality, morbidity, and health care expenditure [21]. The high prevalence of key risk factors is highlighted in national surveys and regional studies [5]. Office workers are at a higher risk of developing NCDs as the nature of their work leads them to be sedentary during work hours and their dietary intake does not follow local or global recommendations [7,8]. When a group of people with common risk factors are gathered in one place, there is a window of opportunity for health interventions to mitigate these risk factors. Furthermore, health education and promotion interventions through the mainstream preventive health sector hardly ever reach office workers. Therefore, this trial focused on an intervention to change the dietary behavior of office workers in a selected administrative district (Galle) in Sri Lanka. The intervention was planned based on SOC theory and was implemented as a stage-matched intervention at the individual level. Thus, it provided participants with the best-matched intervention. Therefore, this protocol provides valuable insights into several areas, such as dietary interventions for office workers based on behavioral theories and stage-matched interventions. Furthermore, it will enrich the existing scientific knowledge with information on the planning and implementation of interventions in a low- to middle-income country.

This study was designed as a cluster randomized trial with equal allocation of clusters to the intervention and control arms. This protocol was developed to implement an intervention aimed at changing the dietary behavior of office workers.

## Methods

### Design

This study was a cluster randomized intervention trial with a parallel-group design. It lasted 3 months (12 weeks), and the intervention’s superiority in changing dietary behavior among office workers was assessed compared to the control group. Data for the baseline or preintervention assessment were extracted from a cross-sectional study, which was conducted before the commencement of the intervention to assess the dietary intake of the same study sample, and postintervention data collection was conducted at the end of 3 months. The intervention schedule and enrollment and assessment time points are illustrated in Figure 1.

**Figure 1 figure1:**
[figure not shown]
Flow of participants through the study.

### Study Setting

This study was conducted in 20 selected government offices in the Galle district. Offices were purposefully chosen to ensure similarity in office functions and the number of clerical-type workers. The minimum travel distance between 2 given offices was more than 5 km. An office with 30 clerical-type workers was defined as a cluster to enroll in the study.

### Study Population and Eligibility Criteria

Clerical workers at government offices selected as clusters were enrolled as study participants. Workers involved in any physical exertion as part of their duties and workers put on specific diet plans for medical reasons were excluded from the study.

### Sample Size

The sample size for the trial was calculated using the following formula for estimating the difference between 2 proportions [22]. A 5% α error was allowed, and 80% power was expected when calculating the sample size. A 50% increase in the factor of interest was assumed, as a meta-analysis on behavioral modifications showed an increase in factors of interest by 50%. As the 2015 STEPS survey reported that only 28% of the population had met the recommended number of fruit and vegetable servings [5], 0.3 was assumed as the baseline proportion for the recommended fruit and vegetable intake and was expected to increase by 50% at the end of the intervention. Therefore, 0.45 was assumed as the proportion in the intervention arm after the intervention.

Substituting the aforementioned values in the equation, the calculated minimum sample size in each arm of the cluster randomized trial was 160.

Design effect for cluster sampling was calculated assuming a cluster size of 30 and an intraclass correlation of 0.02 because the intraclass correlation coefficient in human studies usually lies between 0.01 and 0.02. A study among office workers reported an intraclass correlation coefficient of 0.02 [23]. Substituting the aforementioned values in the equation, the design effect for this study was 1.58.

Therefore, the minimum sample size for each arm was 253. After accounting for a 10% dropout rate, the study’s minimum sample size per arm was 280 office workers. Thus, the minimum sample size in the intervention and control groups was 560 office workers.

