### Randomization

After baseline data collection, all selected clusters were randomized into 2 arms. The principal investigator or data collectors did not know whether a particular cluster belonged to the control or intervention arm at baseline data collection, which minimized observer bias during this stage.

All selected clusters were arranged in ascending alphabetical order, and a number was assigned to each cluster. An online randomization sequence generator assigned the numbers 1 to 20 into 2 arms. The intervention arm had 10 numbers, and the control arm had 10 numbers. Clusters with allocated numbers were randomly assigned to the intervention and control arms.

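### The stated 80% power makes no allowance for only 20 randomised offices; at the protocol's own inputs the stated minimum sample gives about 78%

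*Protocol article*

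**What the plan says.** The Sample Size section sizes the trial on a comparison of two proportions with a 5% type I error, and says that "80% power was expected when calculating the sample size". For the control value it reports that "the 2015 STEPS survey reported that only 28% of the population had met the recommended number of fruit and vegetable servings", and then states that "0.3 was assumed as the baseline proportion for the recommended fruit and vegetable intake". A 50% relative increase leads to the alternative: "0.45 was assumed as the proportion in the intervention arm after the intervention".

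The result is 160 per arm. With 30 per office and an ICC of 0.02, the design effect is 1.58, which gives 253 per arm, and 10% dropout raises this to 280. The section places the ICC in human studies between 0.01 and 0.02 and uses the upper value, citing a study of office workers.

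On allocation, the Randomization section says: "The intervention arm had 10 numbers, and the control arm had 10 numbers". The Sample Size section does not mention any adjustment for the small number of offices.

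**The concern.** The design effect inflates the variance of the estimated difference, but it does not change the reference distribution. With 10 offices per arm, the between-office variance is estimated on about 2 × 10 − 2 = 18 degrees of freedom, and a sample size built on 1.96 and 0.84 ignores that. Separately, the control proportion was rounded up from the cited 28% to 30%. Because the effect is set as a relative increase, this widens the target difference from 14 to 15 percentage points and lowers the required number.

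Both steps make the stated power more favourable. A null result on the fruit and vegetable outcome would then be read against an 80% claim that the stated minimum does not quite reach.

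**Working it through.** **Inputs.** All are from the Sample Size section, except the number of offices (Randomization): two-sided α 0.05 (sidedness is not stated, but two-sided reproduces the figure), power 0.80, p1 = 0.30, p2 = 0.45, ICC 0.02, 30 per office, 10% dropout, 10 offices per arm.

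**Step 1: reproduce the protocol's figures.**
- Variance sum: 0.30 × 0.70 + 0.45 × 0.55 = 0.4575.
- n = (1.960 + 0.842)² × 0.4575 / 0.15² = 159.6, that is 160.
- Design effect: 1 + 29 × 0.02 = 1.58, and 160 × 1.58 = 252.8, that is 253.
- Dropout: 253 / 0.9 = 281, against the stated 280, which is close enough.
- Power at 253 per arm with normal quantiles: effective n = 253 / 1.58 = 160.1; standard error = √(0.4575 / 160.1) = 0.0535; 0.15 / 0.0535 = 2.81; power 80.1%.

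The stated chain is therefore correct on its own terms.

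**Step 2: change only the reference distribution.** Use a noncentral t with 18 degrees of freedom, critical value 2.10 and noncentrality 2.81. Power is 75.6%.

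**Step 3: match the design effect to the number analysed per office.** The stated minimum of 280 per arm less 10% leaves 252, or 25.2 per office over 10 offices. The design effect is 1 + 24.2 × 0.02 = 1.484 and the effective n is 252 / 1.484 = 169.8. The standard error is 0.0519 and the noncentrality 2.89. Power is 82.4% with normal quantiles and **78.0%** with t on 18 degrees of freedom. Using 30 per office in the design effect was slightly conservative, and this offsets about half of the loss in step 2.

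**Step 4: 30 enrolled per office.** That is 300 per arm; less 10%, 270 remain (27 per office, design effect 1.52, effective n 177.6). Power with t on 18 degrees of freedom is 79.8%.

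**Step 5: sensitivity at the cited 28%, keeping the 50% relative increase.** p2 = 0.28 × 1.5 = 0.42, and the variance sum is 0.2016 + 0.2436 = 0.4452.

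| Analysed per arm | Design effect | 30% vs 45%, t(18) | 28% vs 42%, t(18) |
|---|---|---|---|
| 253 | 1.58 (held) | 75.6% | 70.9% |
| 252 (25.2 per office) | 1.484 | 78.0% | 73.4% |
| 270 (27 per office) | 1.52 | 79.8% | 75.3% |

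**Step 6: what else moves the result.**
- Keeping the absolute 15 points (28% vs 43%) at 253 and design effect 1.58 gives 81.1% with normal quantiles and 76.6% with t. The rounding costs power only if the relative increase is what is held.
- At ICC 0.01, the lower end of the protocol's range, with 253 and 30 per office (design effect 1.29), t on 18 degrees of freedom gives 83.6% at 30% vs 45% and 79.4% at 28% vs 42%.

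**The case against.** The strongest defence is that nothing was miscalculated: the inputs are disclosed, and they give 80% by a conventional formula. That stands. What is missing is a small-sample allowance, and its effect is smaller than the effect of moving the ICC within the protocol's own range.

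The choice of 0.30 is also open to view, since the 28% appears in the same section. It is an optimistic planning value and not a slip.

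Three stronger readings are tempting, and the document does not support them.

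- A reader might infer that the true power is 71% to 76%. Those figures pair 253 per arm with a design effect for 30 analysed per office, whereas 253 over 10 offices is about 25 each. The 71% also needs the 28% baseline on top of the t distribution.
- A reader might infer that the design falls short of 80% even at full recruitment. With 30 enrolled per office and 10% loss, the degrees-of-freedom point alone leaves 79.8%, which is 80% for practical purposes.
- A reader might take the Background's statement that "nearly 75% of male and female individuals were not consuming the recommended amount of fruits and vegetables" as a 25% baseline and derive still lower power. It is a rounded narrative phrase, compatible with the more precise 28% in the Sample Size section, so a 25% scenario has no firm basis.

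One further limit applies. The 18 degrees of freedom presuppose an analysis that respects office-level randomisation. The Data Analysis section names binary logistic regression and does not state how clustering is handled. A test that ignored clustering would not rescue the 80%, because the sample size calculation itself assumes an ICC of 0.02.

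**Conclusion.** The point holds in a modest form. The 80% rests on normal quantiles although 20 offices are randomised. At the protocol's own proportions and ICC of 0.02, the stated minimum gives about 78% with t on 18 degrees of freedom; the range is 75.6% to 79.8%, depending on the design effect and the number analysed per office. With the cited 28% and the same relative increase, it is about 73% at the stated minimum and 75% at 30 per office.

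These figures assume a two-sided 5% test, unpooled variance and equal office sizes. At ICC 0.01 the shortfall at 30% vs 45% disappears. They concern the planned numbers and the fruit and vegetable proportion on which the trial was sized; they do not address actual recruitment or the choice of endpoint. Severity: minor.

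**What to change.** Restate the planned power for the stated minimum as about 78%, using t on 18 degrees of freedom and a design effect that matches the number analysed per office. Show about 73% as the sensitivity at the cited 28% with the same 50% relative increase.

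In the results paper, use 18 degrees of freedom for any detectable-difference statement on the fruit and vegetable outcome. Take that outcome's baseline proportion and ICC from the 518 workers assessed at baseline, before randomisation. Do not carry the baseline dietary ICC over to stage-of-change progression: progression is a change and has no baseline value, so baseline diet supplies neither its ICC nor its control rate.

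The cost is a sentence and a recalculation, and a slightly less favourable stated power. No participants, data or trial procedures are affected.

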### Recruitment

Multistage cluster sampling was used to recruit study participants. A cluster was defined as an office with at least 30 clerical-type workers. A total of 20 clusters were selected purposefully to fulfill three requirements as follows: (1) the nature of the work carried out in the offices should be similar, (2) travel distance between any selected offices should be 5 km, and (3) the offices should have 30 to 40 clerical-type workers.

An exhaustive list of government offices established in the Galle district was prepared after obtaining information from the chief secretary’s office (Southern Province) and the District Secretariat (Galle district). Information about the functions of each office was obtained from the district secretary and the chief secretary’s office. Offices that carried out similar activities were short-listed. Offices were then short-listed again depending on the number of clerical-type workers (30 to 40). The travel distance between each office was then assessed using the direction function in Google Maps. If the travel distance between 2 or more offices was less than 5 km, the office with the highest number of clerical-type workers was selected, excluding the rest. Short-listing aimed to select 20 offices that matched the recruitment criteria. However, the ultimate short list contained only 19 offices because of inadequate distance between 2 offices. The distance requirement was then reduced to at least 5 km from more than 5 km.

Within the clusters, participants were selected using a series of random numbers. Once clusters were selected, the relevant offices were contacted, and a study coordinator was appointed for each office. The coordinator obtained a list of clerical-type workers’ names. The workers’ names were arranged alphabetically, and a number was assigned to each. An web-based random number generator selected 33 numbers from the list. The workers assigned the selected numbers were invited to participate after assessing their eligibility according to the inclusion and exclusion criteria. They were informed of the study and the data collection date through the office coordinator.

On the day of data collection, the selected participants were informed about the study, and the purpose, risks, and benefits were explained. The workers who provided consent were recruited for the study

### Participant Timeline

Data from a cross-sectional study were extracted for all selected government offices in the Galle district, and 2 months were allocated for this. Data on participants’ demographic profiles, health conditions, dietary practices, SOC, and dietary intake were extracted from the aforementioned cross-sectional study as preintervention or baseline data for the interventional study. Randomization was conducted following the baseline data collection. Once randomization was done, the principal investigator and resource person for lectures visited each office in the intervention arm on a prescheduled day. All participants in the study were informed of the date beforehand. The principal investigator applied the intervention, and the resource person delivered lectures. If any participant missed the initial intervention, a second visit was arranged to achieve maximum participation. The initiation of the intervention in all 10 selected offices was completed within 1 month. Monthly assessments and lectures were conducted on prescheduled days following one, two and three months of the initiation date for each office. However, a second day was not arranged for monthly assessments and lectures. A postintervention assessment was conducted at the end of 3 months. The date for the postintervention evaluation was given to all participants to ensure that they took part in the assessment. If any participant missed the postintervention assessment, another day was arranged. Figure 1 shows the flow of participants through the intervention process.

### Data Collection

After selecting offices for the study, administrative approval was obtained from relevant authorities. The principal investigator met or contacted the office heads (divisional secretaries and chairmen of local authorities) to obtain permission for data collection. Thereafter, one senior worker, either a development officer or management assistant, was appointed as the coordinator for the study from each office. The list of eligible office workers was obtained through the coordinator. Thereafter, 33 workers were selected from each office as described in the Recruitment section. A date for data collection was fixed, and all selected participants were informed through the coordinator, requesting their presence at the office on the fixed date.

The principal investigator explained the purpose and nature of the study to potential participants. Information sheets and consent forms (Multimedia Appendix 1) were distributed among all eligible participants invited to take part in the study. The self-administered questionnaire (Multimedia Appendix 2) was then distributed among participants who consented to the study.

Three trained data collectors collected the data. Participants were allowed to ask questions and supported by the data collectors. After completion of data collection, the data collectors retrieved the filled-out questionnaires and checked them for completeness.

Furthermore, participant-reported health-related data were verified by referring to available clinical records as participants were asked to keep clinical records with them before data collection.

The data collectors also measured the weight and height of the participants using a calibrated weighing scale and stadiometer, and the measurements were recorded following the standard procedure described by Greenwood et al [24].

The assessment of the SOC was conducted using a staging algorithm which was originally used in the well-known “5 a day” project and subsequently used by many studies [25-27]. It comprised 4 mutually exclusive branching questions . The responses to the 4 questions were used to determine a participant’s SOC as follows.

The first question was “Do you follow healthy dietary guidelines?” If the answer was “yes,” the participant was asked, “for how long have you practiced your current diet?” (response options: “more than 6 months” [maintenance stage] and “less than 6 months” [action stage]). If the answer was “no,” the participant was asked, “are you seriously thinking of changing to a healthy diet in the next 6 months?” If the answer to the latter was “yes,” the participant was asked, “are you going to change your dietary habits next month?” If the answer was “yes,” the participant was allocated to the preparation stage. If the answer was “no,” the participant was allocated to the contemplation stage. If the answer to the question “are you seriously thinking of changing to a healthy diet in the next 6 months?” was “no,” the participant was allocated to the precontemplation stage.

To minimize bias due to misperception of the diet’s healthiness, the initial question was modified to read the following: “Have you changed your diet by reducing the amount of carbohydrates, salt, and sugar and increasing the amount of fruit and vegetable portions?”

The SOC of a participant was determined by coupling the staging algorithm with dietary assessment as suggested by Greene et al [28]. The perceived SOC reported by the participants was amalgamated with their dietary intake. Participants who followed a diet that met the definition of a healthy diet were assigned to their perceived SOC as reported by them. For example, if a participant reported being in the action or maintenance stages and their diet met the overall definition of a healthy diet, they were allocated to their reported SOC. In contrast, if participants who followed a diet that did not meet the definition of healthy dietary intake reported being in the action or maintenance stage, they were allocated to the preparation stage. This approach is summarized in Table 1.

**Table 1 table1:** Summary of the process of ascertaining the stage of change of the participants.

Staging algorithm result	Type of diet based on 24-h recall	
	Healthy	Unhealthy
Precontemplation	Precontemplation	Precontemplation
Contemplation	Contemplation	Contemplation
Preparation	Preparation	Preparation
Action	Action	Preparation
Maintenance	Maintenance	Preparation

The 24-hour dietary recall was completed for each participant by the trained data collectors through face-to-face interviews and a computer software designed specifically for this study. Participants were asked to recall their food intake the day before the data collection date. Data were collected on a routine office day. Mondays and days after holidays were not scheduled for data collection. At the same time, it was established that participants would have their regular meals on the date selected for dietary recall. Where this was not possible, the nearest day in which they had their regular meals as they did on a routine office day was considered for the dietary recall.

Participants were asked to name all food items and the amounts they consumed between waking up and going to sleep. Data collectors then inquired about the amount of food consumed using household measurements.

Interview materials were used to quantify the intake from different food groups. A picture guide that included all household measuring items (eg, spoons and cups) and food portions obtained through commonly used measurements was used to identify the quantity of each food item consumed (Multimedia Appendix 3). A computer software that can convert household measurements to servings described in the FBGD for Sri Lankans was used to calculate the serving number from each food group (Multimedia Appendix 4).

